#### The control group

The study will be conducted in three stages in the control group. After a recruitment period prior to baseline assessment and randomization, patients in the control group will be arranged to accept IVF/ICSI directly without any other intervention. The participants in this group will receive the GnRH antagonist protocol for COH that is the same as the DKD group. Finally, a 12-week follow-up will be included.

#### General advice

All participants in both groups will be advised to maintain a healthy lifestyle during the study, such as no smoking, no alcohol, low-fat high-protein diets, regular exercise, and to get plenty of sleep.

#### Management of intervention medication (DKD)

All the DKD (water-honeyed pill) will be provided free of charge by the Shanxi Guangyuyuan TCM Co., Ltd. It will be stored at room temperature and dispensed locally at the treating hospital. Patients will take DKD 7 mg twice daily orally from the first day of their menstrual period for 3 months. If the patient has side effects on this dose, it is permissible to reduce the dose to 3.5 mg twice daily. If on completion of the trial, or in case of withdrawal from the study, any unused DKD will be returned to the pharmacy. As DKD is the standard of care within TCM, no special drug accountability is required. Patients will be given a diary and asked to keep a record of their daily medication usage, which is returned to the investigator on completion of the course of DKD treatment. A complete listing of all concomitant medication received during the treatment phase must be recorded in the relevant Case Report Form (CRF).

#### Patient safety and indemnity

DKD is the standard of care within TCM. The TCM hospital in which the DKD is prescribed, and the hospital in which the IVF/ICSI treatment is carried out, provide indemnity for approved clinical research in their institution.

As DKD is the standard of care, no special arrangements need to be put in place in case of adverse events.

In case of emergency, the patient will be provided with a 24-h contact number to call.

### Outcome measures

#### Primary outcome

The primary outcome of the study is ongoing pregnancy rate, defined by at least one intrauterine viable fetal heart beat at 12 weeks of gestation.

#### Secondary outcomes

The secondary outcomes include total gonadotropin dosage; duration of stimulation; cycle cancellation rate; E_2_ and progesterone (P) levels on the hCG trigger day; retrieved oocyte number; high-quality embryo development rate; biochemical pregnancy; as well as some specific endpoints indicative of the ovarian response, such as the change of serum AMH, FSH, E_2_ level. All side effects, safety outcomes and adverse events will also be recorded. All data will be collected using an electronic Case Report Form (eCRF) and will be supervised by an independent statistician from Tianjin CLINDA Medical Technology Co., Ltd.

The standard of high-quality embryo development rate is according to the Istanbul criteria [30] as following: Grade 1 – good rating: 10% fragmentation, stage-specific cell size, no multinucleation. Grade 2 – fair rating: 10–25% fragmentation, stage-specific cell size for majority of cells, no evidence of multinucleation. Grade 3 – poor rating: severe fragmentation (> 25%), cell size not stage specific, evidence of multinucleation.

#### Adverse events

During the study, all the details including all adverse events, such as swelling and aching of the gums, oral ulceration, constipation, and ovarian hyperstimulation (OHSS) will be recorded in detail. Serious adverse events will be immediately reported to the principal investigator, and appropriate measures will be initiated instantly.

The Ethics Committee will determine whether the adverse event is likely to have been associated with the experimental drug, and the sponsor will provide the cost of the treatment associated with the study and the corresponding financial compensation.

#### Data management

All data will be collected using an eCRF and will be supervised by an independent statistician from Tianjin CLINDA Medical Technology Co., Ltd., and will be completed and recorded on the paper and eCRF. Paper files will be kept in a locked filing cabinet in the treating hospital. Electronic documents will be stored in a password-protected computer, with access restricted to the principal investigator. All research documents will be preserved for at least 5 years after publication.

#### Quality control

All clinicians involved with the trial will be fully trained in the trial methodology. After the clinician has recruited the first patient the CRF will be reviewed by the researcher to ensure that it has been correctly completed.

To ensure trial quality and reliability, a clinical trial monitor from Tianjin Taicheng Yaozhong Biomedical Technology Co., Ltd. will verify all of the process details at when the experiment is half done and completed. Moreover, the monitor will check the authenticity, accuracy, and integrity of the data.

#### Collecting trial data

At the beginning of the study, blood will be taken for baseline FSH, E_2,_ and AMH, and an ultrasound will be performed to measure the antral follicle (AFC) in both groups. After 3 months of DKD treatment, and before commencing IVF/ICSI, the same data will be collected in the DKD group. These blood tests will be assayed within each participating center. The AFC will be performed by the treating team.

After the IVF/ICSI treatment cycle has been completed, the total gonadotropin dosage, duration of stimulation, E_2_ and P  levels on hCG trigger day, cycle cancellation rate, retrieved oocyte number, high-quality embryo rate, and biochemical pregnancy will be recorded.

If the patient is pregnant, the presence or absence of a fetal heart will be noted 4–6 weeks after the embryo transfer, and the ongoing pregnancy rate at 12 weeks of gestation, and the miscarriage rate will be recorded during the follow-up.

Trained nurses will take the blood samples, and ultrasound physicians, independent of the researchers, will perform the ultrasonography.

### Statistical analysis

Statistical analysis will be performed using SAS 9.2 software package. Intention-to-treat analysis will be applied to minimize bias due to dropouts, and reasons for which patients have dropped out will be recorded in detail and analyzed after the trial. Multiple imputation analysis will be used for missing data. Normally distributed continuous variables are reported as means and standard deviations, non-normally distributed continuous variables are reported as medians and ranges, and the count data will be described by frequency, percentage and constituent ratio. Results will be presented as point estimates and 95% confidence intervals; the level of significance will be set at 5%.

Baseline characteristics of dropout patients will be compared with those who did not. As age is a crucial factor for infertility and the effect of treatment, a simple linear model with age as a covariate will be used to analyze continuous outcomes, and a binomial generalized linear model (GLM) with age as a covariate for binary outcomes.

To compare the efficacy of DKD for female infertility with POR with the control group, the Pearson’s chi-squared test will be applied to compare frequencies between groups such as the ongoing pregnancy rate, cycle cancellation rate, high-quality embryo rate. And the *t* test will be performed to compare continuous parameters (retrieved oocyte number, gonadotropin dosage, E_2_ and P level on the hCG trigger day, etc.) between the groups. In the treatment group, the rank sum test or paired-sample *t* tests will be used to compare the indicators pre- and post treatment; for instance, basic FSH, E_2_ level, and AMH level.

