The purpose of this study is to evaluate ongoing viable pregnancy rate at 12 weeks’ gestation and related indicators of ovarian response in female fertile who have a predicted POR having immediate versus delayed IVF/ICSI after 3 months of DKD pre-treatment.

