## Methods/design

### Study design

This study is a multicenter, randomized controlled, parallel-group, phase III, superiority study. Eligible participants will be randomly assigned to the DKD group or the control group with a 1:1 ratio. The study flow is shown in Fig. 1. The study will be conducted in four stages in the DKD group and in three stages in the control group. Participants in the DKD group will receive DKD pre-treatment for 3 months before IVF/ICSI, while in the control group, participants will receive IVF/ICSI immediately without any other intervention.

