#### Sample size

The sample size calculation is based on the ongoing pregnancy rate. Studies indicated that ongoing pregnancy rate of female infertility with POR undergoing IVF/ICSI cycles was 12.5% to 15.8%, with an average of 13% [23–27]. We hypothesized that a supplementation of DKD can increase the ongoing pregnancy rate to 26%.

According to the sample size of the estimation formula [28]:$$ n\kern0.5em =\kern0.5em {\left({Z}_{\alpha }+\kern0.5em {Z}_{\beta}\right)}^2\kern0.5em \left[{P}_1\left(1-{P}_1\right)+{P}_2\left(1-{P}_2\right)\right]/{\left(\varepsilon -\delta \right)}^2, $$where *n*_1_ = *n*_2_ = *n*/(1–20%), *Z*_α_ = Z_0.05_ = 1.64, *Z*_β_ = *Z*_0.8_ = 0.84, *P*_1_is the ongoing pregnancy rate of the treatment group = 0.26, *P*_2_ is the ongoing pregnancy rate of the control group = 0.13, and *ε* is the difference of *P*_1_ and *P*_2_. Assume the superiority margin is 0 (*δ* = 0).

For 80% power to detect a difference between the experimental arm and the control arm at a one-sided 5% type I error rate, we need 112 per arm. This assumes standard sample size formulae for binary outcomes using a normal approximation [28]. To account for a 20% dropout rate, we will recruit 139 patients per arm. Considering the number of outpatients in each centre will be fluctuating during the trial; therefore, we use a dynamic randomization method to generate random numbers, and so there is no strict restriction on the number of participants in each centre.

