#### Discontinuation criteria

Reasons for discontinuation of treatment may include, but are not limited to, the following: (1) participants become pregnant during the trial, (2) participants who have experienced some complications or serious side effects), (3) participants who do not comply with the DKD regimen, as defined by less than 80% or more than 120% of the prescribed amount; using prohibited drugs as described in the protocol, such as contraceptive drugs, ovulation-stimulating medicine, glucocorticoids etc., (4) participants who request to withdraw from the trial.

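### Multiple imputation has no exception for women who leave before IVF; imputing them from completers would estimate a no-dropout effect, not the ITT effect of immediate versus delayed IVF, and would probably favour DKD

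*Protocol article*

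**What the plan says.** All references are to the protocol article.

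- **Statistical analysis** sets the population, "Intention-to-treat analysis will be applied to minimize bias due to dropouts", and the missing-data rule, "Multiple imputation analysis will be used for missing data". The rule makes no exception for the primary outcome or for women who never reach embryo transfer.
- **Primary outcome** is ongoing pregnancy, "defined by at least one intrauterine viable fetal heart beat at 12 weeks of gestation". It is not tied to a trial transfer.
- **Background** states the question as women "having immediate versus delayed IVF/ICSI after 3 months of DKD pre-treatment". This compares two strategies, and the delay is part of one of them.
- **Study design** gives the arms different paths: "Participants in the DKD group will receive DKD pre-treatment for 3 months before IVF/ICSI", whereas in the control group "participants will receive IVF/ICSI immediately without any other intervention".
- **Discontinuation criteria** include "participants who do not comply with the DKD regimen, as defined by less than 80% or more than 120% of the prescribed amount", which can arise only in the DKD arm. They also list becoming pregnant.
- **Sample size** handles loss by inflation alone: "To account for a 20% dropout rate, we will recruit 139 patients per arm". The assumed rates of 26% and 13% are not reduced for dropout.
- **Collecting trial data** describes outcome recording around the IVF cycle and after transfer. It does not describe how pregnancy status is obtained for a woman who leaves before IVF.

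**The concern.** In a comparison of immediate with delayed treatment, failing to reach IVF is one of the ways in which delay can cost a pregnancy. A woman who leaves during the DKD phase, has no transfer and does not conceive otherwise is a failure of the assigned strategy. If she is instead coded as missing and imputed from women who completed IVF, she receives roughly the completers' chance of pregnancy. The estimand is then a hypothetical one, the effect had nobody dropped out, although the analysis is labelled intention-to-treat.

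The arms are not equally exposed. Only the DKD arm has a 3-month window before IVF, and only that arm can have women discontinued for DKD non-compliance or for DKD side effects. The trial is open-label, and its Discussion describes these patients as unwilling to lose 3 months on placebo. Greater pre-IVF loss in the DKD arm is therefore a reasonable expectation. At stake are an overstated benefit and, if DKD does nothing, a harm from delay that the analysis cannot show.

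**Working it through.** **Inputs.** From Sample size: rates 0.26 and 0.13, z values 1.64 and 0.84, 20% dropout, 139 per arm. Assumed, because the article does not give them: the dropout in each arm (dT for DKD, dC for control), that all loss is before IVF, that no leaver conceives, that 26% and 13% are the rates among women who start IVF, and that imputation draws on completers in the same arm.

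**1. The plan's own figure.** n = (1.64 + 0.84)² × [0.26×0.74 + 0.13×0.87] / 0.13² = 6.1504 × 0.3055 / 0.0169 = 111.18, so 112. Then 111.18 / 0.8 = 138.98, so 139. Both figures reproduce. Dropouts are treated as lost information, at unchanged rates.

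**2. Pregnancies credited.** At 20% loss, 0.20 × 139 = 27.8 DKD women leave. Imputing them at 26% credits 27.8 × 0.26 = 7.2 pregnancies to women with no transfer. The control arm is credited between 0 (no loss) and 27.8 × 0.13 = 3.6 (20% loss).

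**3. If DKD works as hypothesised.** Imputation targets 0.26 − 0.13 = 13.0 points whatever the loss. Among all randomised women the difference is 0.26(1 − dT) − 0.13(1 − dC). Power is for 139 per arm, by the normal approximation with pooled variance under the null, leavers counted as not pregnant.

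| Loss DKD / control | All randomised | Difference (points) | Power, one-sided 5% | Power, two-sided 5% |
|---|---|---|---|---|
| 20% / 0% | 20.8% vs 13.0% | 7.8 | 54% | 41% |
| 20% / 5% | 20.8% vs 12.35% | 8.5 | 60% | 47% |
| 20% / 10% | 20.8% vs 11.7% | 9.1 | 66% | 54% |
| 20% / 20% | 20.8% vs 10.4% | 10.4 | 77% | 67% |

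A simulation of 20,000 trials gave 60% and 48% at 20%/5%, and 78% and 68% at 20%/20%. In the same simulation, within-arm imputation (20 imputations, Rubin's rules) had one-sided power of 82% and 80%.

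**4. If the strategies give equal rates per woman randomised.** The DKD completers' rate is then 0.13(1 − dC)/(1 − dT), and imputation shows a gain of that value minus 0.13.
- 20%/0%: 0.1625 − 0.13 = 3.25 points
- 20%/5%: 0.1544 − 0.13 = 2.4 points
- 20%/10%: 0.14625 − 0.13 = 1.6 points
- 20%/20%: 0

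The simulated one-sided 5% error rate is about 17%, 13%, 10% and 5% respectively.

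**5. If DKD has no effect among women who start IVF.** Imputation shows 0. The strategy difference is 0.13×0.80 − 0.13 = −2.6 points at 20%/0%, and 0.13×0.80 − 0.13×0.95 = −1.95 points at 20%/5%.

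**6. When the direction reverses.** Suppose a share s of DKD leavers left with an ongoing pregnancy and were set to missing. The all-randomised DKD rate is 0.80×0.26 + 0.20s, which exceeds the imputed 26% once s is above 0.26.

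**The case against.** A reader might infer that the plan will certainly credit pregnancies to women who had no transfer, and that the error must favour DKD. The article does not support that.

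- **Coding is not stated.** Imputation is reserved for missing data, and nothing says that a woman without a transfer is coded as missing. An analysis plan that is not shown could code her as not pregnant. Nor does the article specify a within-arm model or a missing-at-random assumption. This stands, and it makes the finding conditional. It does not remove it: the stated rule has no exception, the sample size treats dropouts as lost information, and outcome collection is described only around the IVF cycle. Imputation is the natural reading.
- **The loss pattern is assumed.** One 20% figure covers both arms. With equal loss there is no bias under the null, although a real effect is still overstated (13.0 against 10.4 points).
- **A leaver's outcome is not always known.** The primary outcome is not restricted to trial transfers, and every participant was planning IVF/ICSI. A woman who stops DKD may conceive naturally or be treated elsewhere. This stands, and it is why follow-up belongs in the fix.
- **Pregnancy is itself a discontinuation reason.** If such women were set to missing, the error could run against DKD (step 6).
- **Counting leavers as failures has its own bias.** If follow-up stops at withdrawal, later pregnancies are missed, mostly in the arm with more loss. This also stands unless leavers are followed.

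It would also be loose to call the imputed result per-protocol. Imputation keeps all randomised women; what changes is the estimand.

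**Conclusion.** The concern holds in conditional form. If women who leave before IVF are imputed from completers, the analysis does not answer the article's own question about immediate versus delayed IVF.

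With 20% DKD loss, the overstatement of a real effect runs from 2.6 points (13.0 against 10.4, equal loss) to 5.2 points (13.0 against 7.8, no control loss). If the strategies are truly equal, the false gain runs from 0 to about 3.3 points. These sizes assume that all loss is before IVF, that no leaver conceives, and that imputation is within arm.

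That the bias favours DKD is probable from the design, not established. The rule should be changed because it leaves the handling of the primary outcome open at the point where the arms differ by design.

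**What to change.** Replace the general rule, for the primary outcome, with the following:

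1. Analyse all randomised women in their assigned arms.
2. Ascertain ongoing pregnancy status at 12 weeks for everyone, including women who discontinue, however the pregnancy was conceived. Women discontinued because of pregnancy are followed and their outcome observed, never imputed.
3. Count a woman with no transfer and no known pregnancy as not pregnant. Cancelled cycles are already recorded, so naming them here is only clarification.
4. Keep multiple imputation for women whose status is truly unknown, for example those lost after transfer or after a positive hCG, or known to have been treated elsewhere with no obtainable result.
5. Report imputation of all dropouts as a sensitivity analysis, with dropout shown by arm and by whether it came before or after the start of IVF.

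**Cost.** The change needs a wording revision and brief outcome follow-up of leavers. Stated power also falls: about 77% one-sided and 68% two-sided at 20% loss in both arms, and about 60% and 48% at 20%/5%, if leavers do not conceive. The sponsor should see those figures now.

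### Two unranked analyses are prescribed for the primary outcome, an age-adjusted binomial model and a plain chi-squared test; the same conflict affects the continuous outcomes, and neither analysis uses baseline AFC

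*Protocol article*

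**What the plan says.** The primary outcome is binary: ongoing pregnancy, judged by a viable fetal heart beat at 12 weeks (Primary outcome).

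The Statistical analysis section then makes two assignments in consecutive paragraphs.

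- **Adjusted.** Giving as its reason "As age is a crucial factor for infertility and the effect of treatment", it prescribes a linear model with age for continuous outcomes and "a binomial generalized linear model (GLM) with age as a covariate for binary outcomes". No endpoint is named or excluded, so the primary outcome is covered. No link function is given.
- **Unadjusted.** Under the aim of comparing efficacy, Pearson's "chi-squared test will be applied to compare frequencies between groups such as the ongoing pregnancy rate", with cycle cancellation and high-quality embryo rate also listed. The t test is assigned to oocyte number, gonadotropin dosage and trigger-day E2 and P.

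The section promises point estimates with 95% confidence intervals. It does not say which analysis is primary, which is supportive, or what follows if they differ. Age is the only covariate named. Collecting trial data states that AFC is measured at the start in both groups, and Inclusion criteria uses a low AFC as one of three features predicting poor response.

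**The concern.** This is a conflict between two stated prescriptions for the same endpoint, which is different from a detail left for later. Three things follow.

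1. The two tests can fall on opposite sides of 5%, so the trial's conclusion could depend on which one is quoted. The Discussion acknowledges that the trial is not blinded, which makes a choice of test after the data are seen harder to defend.
2. The effect estimate is undefined. A chi-squared test supplies no estimate by itself, and a binomial model supplies an odds ratio, risk ratio or risk difference according to its link.
3. The protocol accepts prognostic adjustment in principle but stops at age. It leaves out a baseline measure of ovarian reserve that it already collects in every woman.

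**Working it through.** **Reproducing the plan's figure.** Inputs from Sample size: Z values 1.64 and 0.84, P1 = 0.26, P2 = 0.13, margin 0, dropout 20%.

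n = (1.64 + 0.84)² × [0.26 × 0.74 + 0.13 × 0.87] / 0.13² = 6.1504 × 0.3055 / 0.0169 = 111.18, so 112 per arm. Then 111.18 / 0.8 = 138.98, so 139 per arm. Both stated figures reproduce. The formula is an unadjusted comparison of two proportions on the risk-difference scale.

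**What the missing link means.** At the design rates the same result reads as a risk difference of 0.26 − 0.13 = 0.13, a risk ratio of 0.26 / 0.13 = 2.0, or an odds ratio of (0.26/0.74) / (0.13/0.87) = 2.35. An age-conditional odds ratio would differ again from this marginal one.

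**How often the tests differ.** The simulation used 112 per arm and 8,000 trials per scenario, and compared the Pearson test with a logistic model holding one standardised covariate. The logit link and the covariate odds ratios per SD are assumptions, because the document gives neither. Null scenarios used a common rate of 13% or 19.5% (midway between 13% and 26%). All tests are two-sided at 5%.

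| Covariate OR per SD | Chi-squared alone, null (13%; 19.5%) | Either test, null (13%; 19.5%) | Tests disagree at 13% vs 26% |
|---|---|---|---|
| 1.0 | 5.34%; 5.38% | 5.39%; 5.51% | 1.6% |
| 1.3 | 5.26%; 5.28% | 5.50%; 5.62% | 3.1% |
| 1.5 | 5.12%; 5.35% | 5.61%; 5.90% | 4.6% |
| 2.0 | 5.44%; 5.34% | 6.35%; 6.69% | 7.4% |

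The Monte Carlo standard error near 5% is √(0.05 × 0.95 / 8000) = 0.24 points. Part of the excess over 5% belongs to the chi-squared test itself. The part due to having a choice is the either-test column minus the chi-squared column: from 5.39 − 5.34 = 0.05 points up to 6.69 − 5.34 = 1.35 points.

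The sample size rests on a one-sided test ("at a one-sided 5% type I error rate, we need 112 per arm"), so the one-sided 5% results matter too. There the either-test error is 5.3–6.0% and disagreement at 13% versus 26% is 1.4–6.0%.

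A second simulation (139 per arm, 2,500 trials; assumed effects of −0.10 per year of age, 0.25 per follicle and ±0.3 for centre on the log-odds scale) gave an either-test error of 5.1%, against 4.7% for a single test. Its standard error is √(0.05 × 0.95 / 2500) = 0.44 points.

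**What AFC would add.** In the second simulation (13.7% versus 27%), power was 79.3% for chi-squared, 80.2% with age, and 81.2% with age, AFC and centre, a gain of 1.9 points over chi-squared. For oocyte number, a covariate with correlation r removes r² of the residual variance: 0.3² = 9% to 0.5² = 25% for an assumed r of 0.3 to 0.5.

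**The case against.** **The text leans towards chi-squared.** That test is introduced as the efficacy comparison and names the primary outcome, and the sample size formula is unadjusted. An unadjusted test with an adjusted companion is also a common pair. These pointers are fair, but they remain inference: the age model is given its own firm justification, and nothing ranks the two. A separate analysis plan may settle the matter, but as the article stands it fixes two answers to one question.

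**The effect is small.** This stands. With an assumed −0.10 per year and an age SD of about 3.5–3.75 years, the odds ratio per SD is exp(0.35) to exp(0.375), about 1.4–1.45. The excess due to choice is then well under one point. The tests are highly correlated, and the 5.1% result cannot be told from nominal.

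**Leaving out AFC is not an error of validity.** This also stands. Omitting a prognostic covariate does not bias a randomized comparison. Eligibility narrows the range of AFC, which may weaken its correlation with outcome, and the assumed strengths have no source in the document.

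**Two stronger readings that the document does not support.**

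- A reader might infer from "These blood tests will be assayed within each participating center" that trigger-day E2 and P are assayed locally and vary by centre. The sentence refers to FSH, E2 and AMH taken at baseline and again after DKD. Trigger-day E2 and P come in the next paragraph with no assay site, and no value is said to vary by centre.
- A reader might infer from "we use a dynamic randomization method to generate random numbers" that centre is a balancing factor which the analysis then ignores. The reason given is fluctuating outpatient numbers, and the balancing factors are not named.

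**Conclusion.** The point holds. The protocol prescribes two analyses for the primary outcome, and two for its continuous outcomes, without ranking them, and it leaves the adjusted effect measure undefined. That conflict can be read directly from the text and needs no assumption.

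Its numerical size does rest on assumptions. Disagreement on significance occurs in about 2–7% of trials at 13% versus 26%, and the two-sided type I error is about 5.1–6.7% if either test may be reported. Both depend on assumed covariate odds ratios per SD of 1.0 to 2.0 or comparable assumed effects, and on a logit link. The inflation is modest. The weightier consequence is that neither the deciding test nor the estimate to be reported is fixed in an open-label trial.

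The unused AFC is a secondary matter of efficiency: about two points of power for the primary outcome, and possibly more for oocyte number, under assumed effects. The stated sample size is not in question here; it reproduces.

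**What to change.** Name one primary analysis before any outcome comparison by arm:

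- **Model.** A binomial GLM with logit link, containing treatment, age, baseline AFC, centre and any other factor used in the dynamic randomization. List those factors.
- **Estimate.** A standardised (marginal) risk difference with 95% CI, obtained by averaging the model's predicted risks under each arm over all randomized women. This matches the scale on which the trial was sized.
- **Covariate timing.** Use age and AFC as measured at the start in both arms. AFC is measured again after DKD in that arm only, and the later value must not enter the model.
- **Supportive analysis.** Keep the chi-squared test and label it supportive.
- **Continuous outcomes.** Use linear models with the same covariates in place of plain t tests for oocyte number, gonadotropin dosage and trigger-day E2 and P.

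Keep the covariate list short. At 139 per arm the design rates give 139 × (0.13 + 0.26) = 54.2 expected pregnancies. With treatment, age, AFC and two terms for three centres, that is 54.2 / 5 = 10.8 events per term.

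The cost is wording only. AFC, age and centre are already available, and the sample size need not change. Trial status reports 40 of the planned 278 women recruited, so the choice could be fixed early.

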#### Randomization and allocation

Eligible participants will be randomly assigned to the experimental group (DKD for 3 months, then IVF/ICSI) or the control group (immediate IVF/ICSI) in a 1:1 ratio by central randomization performed by an independent statistician from Tianjin CLINDA Medical Technology Co., Ltd. Random numbers will be generated by using dynamic randomization on an online computer, which will generate a randomization schedule. Recruitment, allocation, instructions how to take DKD, and study investigations will be carried out by the study investigators. The IVF/ICSI is carried out by the treating team.

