### Intervention

#### DKD group

The study will be conducted in four stages in the DKD group. After a recruitment period prior to baseline assessment and randomization, DKD (water-honeyed pill) will be given to patients in the experimental group 7 g twice daily orally from the first day of their menstrual period, for 3 months. If the participant has side effects on this dose, it is permissible to reduce the dose to 3.5 g twice daily. After that, participants will undergo their IVF/ICSI cycle. Finally, a 12-week follow-up will be included.

COH prior to IVF/ICSI will be initiated on day 3 of the menstrual cycle. All participants will receive a fixed initial daily follicle-stimulating hormone (FSH) (Gonal F, Merck Serono SA, Switzerland) dose of 300 IU subcutaneously for the first 5 days [29]. Thereafter, the daily dose will be adjusted up or down according to follicular response and serum estradiol (E_2_) level, with 450 IU as the maximum daily dose allowed. Participants will receive a gonadotropin-releasing hormone (GnRH) antagonist (Cetrorelix Ac, Merck Serono, Darmstadt, Germany, or ORGALUTRAN, Merck, Kenilworth, NJ, USA) when the dominant follicle reaches 14 mm in diameter or serum E_2_ level higher than 350 pg/ml, at a dose of 0.25 mg daily subcutaneously throughout the remainder of the stimulation period. Triggering of final follicular maturation is performed as soon as one or more follicles are ≥ 18 mm in diameter with 250 μg recombinant hCG (choriogonadotropin-α, Ovitrelle, EMD Serono, Darmstadt, Germany).

Transvaginal ultrasound-guided oocyte retrieval will take place 36 ± 2 h after triggering of final follicular maturation. Oocytes will be inseminated using conventional IVF or ICSI, according to the clinical indication. Embryo transfer will be performed on days 2–3 after oocyte retrieval and a maximum of two embryos will be transferred. Surplus embryos will be cultured until the blastocyst stage and subsequently cryopreserved, for use after trial completion.

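### If embryos are pooled, the chi-squared test on the high-quality embryo rate ignores correlation within a woman and understates the standard error of this secondary outcome

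*Protocol article*

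**What the plan says.** The Statistical analysis section of the protocol article puts three outcomes under one test: Pearson's "chi-squared test will be applied to compare frequencies between groups such as the ongoing pregnancy rate, cycle cancellation rate, high-quality embryo rate". It promises point estimates with 95% confidence intervals and states that "the level of significance will be set at 5" per cent. For binary outcomes it also plans "a binomial generalized linear model (GLM) with age as a covariate for binary outcomes".

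Three other sections bear on the unit of analysis:

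- **Secondary outcomes**: "The standard of high-quality embryo development rate is according to the Istanbul criteria". The grades describe a single embryo, for example "Grade 1 – good rating: 10% fragmentation, stage-specific cell size, no multinucleation".
- **DKD group** (the control group follows the same stimulation protocol): "a maximum of two embryos will be transferred. Surplus embryos will be cultured until the blastocyst stage and subsequently cryopreserved". More than one embryo per woman is therefore foreseen.
- **Randomization and allocation**: allocation, one to one, is made to participants. The randomised unit is the woman.

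The article does not say which grades count as high quality, what the denominator is, or whether the rate is formed per embryo or per woman.

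**The concern.** Pearson's chi-squared test needs independent observations. Ongoing pregnancy and cycle cancellation meet this, with one result per woman. Embryo grade does not, because embryos from one woman share her oocytes, her stimulation cycle and the sperm source, so positive correlation is to be expected. Counting each embryo as a separate observation overstates the information in the data, and chance differences between arms reach significance too often.

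The age-adjusted binomial model does not solve this. Age may explain part of the variation between women, but as described the model has no random effect, no generalised estimating equations (GEE) and no cluster-robust variance.

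At stake is the reliability of the p-value and confidence interval for one secondary outcome.

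**Working it through.** **1. The plan's own figure.** The article gives no embryo-level calculation. Its only sample size concerns ongoing pregnancy: "at a one-sided 5% type I error rate, we need 112 per arm". With 26% versus 13%, Z values of 1.64 and 0.84, and margin 0:

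- n = (1.64 + 0.84)² × [0.26 × 0.74 + 0.13 × 0.87] / 0.13² = 6.1504 × 0.3055 / 0.0169 = 111.18, rounded up to 112.
- 111.18 / 0.80 = 138.98, rounded up to 139.

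Both figures reproduce. They rest on one observation per woman, so this point does not touch them.

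**2. Inputs for the embryo rate.** From the article: nominal level 5%, used two-sided here because results come with 95% intervals and this section gives no sidedness. Assumed, because the article gives neither: embryos per woman m = 2 to 4 and within-woman correlation ρ = 0.1 to 0.4.

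**3. Equal embryo counts.** Design effect DE = 1 + (m − 1)ρ. The naive standard error is 1/√DE of the correct one. Actual two-sided error = 2[1 − Φ(1.96/√DE)].

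| m | ρ | DE | Naive SE too small by | Actual type I error |
|---|---|---|---|---|
| 2 | 0.1 | 1.1 | 5% | 6.2% |
| 2 | 0.3 | 1.3 | 12% | 8.6% |
| 3 | 0.1 | 1.2 | 9% | 7.4% |
| 3 | 0.2 | 1.4 | 15% | 9.8% |
| 3 | 0.3 | 1.6 | 21% | 12.1% |
| 4 | 0.4 | 2.2 | 33% | 18.6% |

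With m = 1 or ρ = 0 the test keeps its 5%.

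**4. Unequal embryo counts.** A simulation used 112 women per arm, Poisson embryo counts (so some women have none), an assumed high-quality probability of 0.40, beta-binomial correlation and 20,000 replicates.

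| Mean embryos | ρ = 0.1 | ρ = 0.3 |
|---|---|---|
| 2 | 7.3% | 11.8% |
| 3 | 8.2% | 15.1% |
| 4 | 9.5% | 18.4% |

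These exceed the equal-count results because women with many embryos dominate the pool. For Poisson counts the design effect is 1 + (mean × ρ). At mean 3 and ρ = 0.3 this is 1.9, which gives 15.5% by the formula against 15.1% simulated.

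**5. After correction.** In the same simulations a variance clustered on the woman gave a type I error of about 5.0–5.5% in every scenario.

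**The case against.** The strongest objection is that nobody has written that embryos are pooled. The rate stands in a list with two per-woman outcomes. If it meant the proportion of women with at least one high-quality embryo, the chi-squared test would be valid. A detailed definition could also sit in a full protocol or analysis plan that is not shown. This stands as a condition on the finding: a reader might infer that the plan definitely treats embryos as independent, and the article does not go that far. It does name the test, however, and a rate built on embryo grades and compared as frequencies most naturally means pooled embryos.

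A second objection is size. These are predicted poor responders, and the Background describes few eggs and many cancelled cycles. Women with one embryo or none contribute no within-woman correlation. That also stands. A reader might take 19% as the expected error, but it needs the highest assumed value of both inputs.

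A third is importance. A reader might infer that a main ovarian-response result, or the trial's conclusion, is at risk. The article lists this outcome among unranked secondary outcomes, and the endpoints it singles out as indicative of ovarian response are the changes in AMH, FSH and E2.

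**Conclusion.** The point holds conditionally. If the high-quality embryo rate is analysed per embryo, neither stated analysis accounts for clustering within a woman, the standard error is too small, and the type I error is above 5%. With equal counts it is about 6–12% for 2–3 embryos per woman and correlation 0.1–0.3, and about 19% for 4 embryos and 0.4. Unequal counts raise it somewhat at the same mean. The direction follows from any positive correlation with more than one embryo per woman. The size rests wholly on assumed inputs and may be modest here.

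The primary outcome is one observation per woman, so its test is not affected.

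One limit applies to any remedy. A per-embryo rate conditions on having embryos and, when pooled, weights women by how many they have, which is itself determined after randomisation. Clustered standard errors correct the variance but do not remove that feature.

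**What to change.** - State the numerator (which grades count as high quality) and the denominator of the rate.
- Analyse the rate with the planned binomial model with age, using standard errors clustered on the woman (GEE with robust variance).
- Limit Pearson's chi-squared to outcomes with one observation per woman, such as ongoing pregnancy and cycle cancellation.
- Optionally, report the number of high-quality embryos per randomised woman, counting zero where there are none, as a supportive analysis. It includes every randomised woman but answers a different question, so it accompanies the rate and does not replace it.

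The cost is a few lines of text and code, with no extra patients or visits. Intervals widen by √DE relative to the naive ones: about 5% at DE 1.1 (√1.1 = 1.05) and about 26% at DE 1.6 (√1.6 = 1.26).
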